### 2.2. Eligibility and Recruitment

This study included individuals (i) aged 65 years or older, (ii) living in the community, (iii) with independent mobility, (iv) with no past medical history of neuropsychiatric conditions (e.g., major depression or bipolar disease), and (v) with no musculoskeletal or cardiovascular disorders that contraindicate participation in moderate exercise and testing. The exclusion criteria included individuals engaged in regular moderate to vigorous exercise training and followed by a nutritionist.

Eligible participants received a complete explanation of the study’s purposes, risks, and procedures. Before data collection, the principal researcher obtained informed consent from interested participants. After the agreement, participants were assigned into a 3-month SHD, MT, combined SHD and MT (SHD + MT), or control group (CG). 

Participants were assessed at baseline and after 3 months of intervention. At baseline, sociodemographic and economic, lifestyle (e.g., tobacco use and habitual physical activity), and general clinical data were collected through a structured questionnaire. Possible changes in these data were assessed in post-intervention assessments. At these two time points, nutritional and food intake evaluations were obtained through multiple reliable tools [33,34,35]: the Mini Nutritional Assessment [36]; physical capacity assessments through the Senior Fitness Test [37] and handgrip strength; a whole-body Dual X-ray absorptiometry (QDR 4500/A, Hologic Explorer, version 12.4, Bedford, MA, USA); a Montreal Cognitive Assessment [38]; the Quality of Life for Old Module (WHOQOL-OLD) [39]; and accelerometry (ActiGraph GT9X Link, Manufacturing Technology, Inc., South Bend, IN, USA) were performed. 

Participants were only informed about which group they belonged to after baseline assessments. Well-trained and skilled researchers executed the same procedures during the two assessment periods.

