#### 2.5.2. Multicomponent Training Group (MT) 

The MT exercise program included 50-min group sessions three times a week on non-consecutive days. The sessions were distributed into three main parts: 8–10 min of warm-up (including walking, postural, mobility, and stretching exercises), 30–35 min of specific training (including balance, coordination, strength, and aerobic conditioning), and 5 min cooldown (breathing and stretching exercises). Exercise prescription followed the main guidelines from the American College of Sports Medicine [42] and the World Health Organization (WHO) [43]—60–80% of maximum heart rate (HRmax) and 50–70% of one-repetition maximum (1RM). 

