Simple, age-adapted, enjoyable, and functional exercises were preferred. Before the training program, a two-month adaptation period was implemented to familiarise the participants with the activities, observe their individual physical needs and promote socialisation among them. The adaptation period maintained a low-intensity range of 40 to 50% HRmax in the aerobic exercises and one set of 12–15 slow repetitions for the strength exercises. The focus was on learning the movements. Exercise intervention prescription, implementation, and evaluation were performed by elderly specialist exercise professionals. Sessions involving a maximum of 25 participants were held in appropriate, safe gymnasiums. Whenever possible, sessions were accompanied by music to promote participants’ involvement and enthusiasm and confer intensity. Balance exercises gradually reduced the base of support and/or reduced sensory input, and included dynamic movements that perturbed the centre of gravity. Additional focus was placed on some easy coordination exercises and conscious control of the body. Four to six multi-joint strength exercises involving major muscle groups were included in each session. The number of repetitions gradually decreased (12–15 to 10–12), but the load increased and could be lifted correctly to volitional fatigue. A rest period was completed between sets. Aerobic endurance was achieved with low-impact exercises, gradually increasing intensity, duration, and HR. The Rated Perceived Exertion (RPE) scale was used to support the exercise intensity control—as medication induces HR alterations and adverse events (such as pain or fatigue). The number of falls was recorded at the end of each MT session. Session attendance was recorded [44] and participants missing more than 12 consecutive sessions (equivalent to one month of detraining) were excluded from the final analyses.

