#### 2.5.3. Combined Sustainable Healthy Diet and Multicomponent Training Group (SHD + MT) 

In this group, participants received the same SHD and MT interventions as the participants of the abovementioned groups: a weekly sustainable and healthy mixed food supply and the additional three group sessions (including the SHD culinary workshop) and one individual telephone interview, in addition to MT 50-min group sessions three times a week on non-consecutive days. 

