#### 2.5.4. Control Group (CG)

The CG received advice on following habitual dietary and PA routines. During the project intervention period, one nutrition session regarding the main principles of a healthy diet and two low-intensity PA sessions were offered to the participants in this group. Weekly telephone contact was conducted to ensure participant retention in the study.

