#### 2.6.2. Secondary Outcomes

##### Dietary Intake Assessment and Nutritional Adequacy

Dietary intake was assessed through a 24-h dietary recall method, including two non-consecutive days, following European Food Safety Authority recommendations [33]. A 24-h dietary recall is a structured interview that collects detailed information (time of day, food source, portion size, and preparation method) about all foods, beverages, and dietary supplements consumed by the participant in the past 24 h. A food model manual with pictures was used to help respondents judge and report portion size and improve accuracy. Information regarding nutritional supplements was also collected (such as type of supplement, name, and dosage).

Energy and nutritional intake, based on the 24 h recalled food data, were estimated using the nutritional analysis software Food Processor®, version SQL 11.11.32 (ESHA Research Inc., Salem, OR, USA).

Additionally, a Food Propensity Questionnaire [34] was applied to estimate usual and seasonal long-term dietary intake based on the preceding year. The frequency of consumption was based on the following food groups: (i) bread- and cereal-based foods, baked goods, and sugar; (ii) vegetables and fruits; (iii) nuts, seeds, and pulses; (iv) meat (including red and processed meat products); (v) fish (including oily-fish) and seafood; (vi) eggs; (vii) dairy products and substitutes; (viii) fruit juices and soft drinks; (ix) alcoholic beverages; and (x) coffee and tea. Seven potential response options were given to estimate the frequency of intake: never, <1 time per month, 1–3 times per month, one time per week, 2–3 times per week, 4–5 times per week, and 6–7 times per week.

The Mediterranean Diet Adherence Screener (MEDAS) Questionnaire [35], validated in the Portuguese population, was used to assess participants’ adherence to the Mediterranean Diet, a traditional gold model of an SHD. The total score of this questionnaire ranges between 1 and 14, in which scores greater than 9 indicate high adherence to the Mediterranean Diet [35,49]. 

Semi-structured questionnaires to measure compliance with the consumption of the food products in the food supply were applied every week. The consumption of different products from the same food groups was also assessed.

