### 2.7. Statistical Analyses

Descriptive results will be expressed as median and inter-quartile range (IQR) or mean and standard deviation (SD), as appropriate, for continuous variables. Discrete variables will be presented as counts and percentages. The minimum threshold value for statistical significance used will be *p* ≤ 0.05.

The normality tests, histogram, and plot distribution will assess the normality of data distribution. Comparative analyses between participants and dropouts will be realised by *t*-test or Mann–Whitney U-test for continuous variables and Pearson-Chi Squared or Fisher exact test for categorical variables to determine whether attrition bias was observed. 

Potential differences among intervention groups in baseline measurements will be evaluated using a one-way Analysis of Variance (ANOVA) or correspondent non-parametric Kruskal-Wallis test. A Pearson Chi-squared or Fisher exact test will be used for between-group comparisons of categorical variables. 

Covariates (e.g., sociodemographic and economic characteristics; clinical history, such as the presence of comorbidities; and daily physical activity) were selected a priori and tested. The confounding variables will be entered as covariates in the ANOVA models. For each model, the contribution of all covariates will be tested separately; only the ones that change the magnitude of the association by at least 10% will be included in the final models. The fit of the models will be determined. Whenever necessary, we will use weighted samples to tackle the bias imposed by differential sampling probabilities.

A delta percentage will be calculated to assess the percentage of change between baseline and post-intervention assessments. An ANOVA or correspondent non-parametric test with repeated measures will be performed for differences in main effects and interactions for each dependent variable. When significant interactions are found, Bonferroni posthoc tests will determine the origin of the differences. Multivariable regression analyses will explore the associations between blood-based markers and metabolomics and the secondary outcomes.

Geographical information systems data will be collected. The associations of the primary and secondary outcomes with environmental features will be explored through generalised linear models to understand whether built environment food and PA features lead to statistically significant differences in participants’ dietary and exercise routines.

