Some challenges to this study must be recognised. Firstly, we anticipate a potential sample with several age-related comorbidities. Secondly, the elderly tend to mainly adopt sedentary behaviours, increasing difficulties in the recruitment process. Based on differences in baseline participant characteristics, a misinterpretation of the primary outcomes and an inability to generalise the results may occur. Considering the main inclusion criteria, the different interventions cannot be generalised to other specific populations. Despite including participants with lower nutritional status or who were inactive, we cannot exclude the possibility that the participants involved in the study were more prone to healthy lifestyle behaviours. Though, this bias was minimised by excluding participants that were engaged in regular physical activity or consulting a nutritionist. Additional research will help identify the most effective diet and exercise intervention protocols for more heterogeneous, non-uniform, and other specific population groups. A cross-over and randomised controlled trial (RCT) design, where the same participant implemented different interventions, would reduce the likelihood of heterogeneity affecting the evaluation of primary outcomes. Initially, our study protocol was thought and designed to be a cross-over RCT. Although, the methodology needed to be adapted due to the beginning of the unpredictable pandemic situation, which occurred simultaneously with the start of the recruitment study and disabled the sample randomisation. The pandemic situation delayed and imposed logistical difficulties in the recruitment process. The lockdown and isolation of this at-risk population group (older adults) affected baseline assessments and the study intervention due to the closure of facilities.

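### Dropping participants who miss more than 12 consecutive training sessions is a post-allocation exclusion stated only for the exercise programme, and it exposes the exercise-versus-non-exercise comparisons to selection bias

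*Protocol article*

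**What the plan says.** The rule closes section 2.5.2, on the training arm: "participants missing more than 12 consecutive sessions (equivalent to one month of detraining) were excluded from the final analyses". The same section sets the schedule: "The MT exercise program included 50-min group sessions three times a week on non-consecutive days". Section 2.5.3 extends the programme to the combined arm, whose "participants received the same SHD and MT interventions as the participants of the abovementioned groups".

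The other arms are handled differently. For the food supply, section 2.6.2 records that "Semi-structured questionnaires to measure compliance with the consumption of the food products in the food supply were applied every week", but the article attaches no exclusion to the answers. For controls, section 2.5.4 says that "Weekly telephone contact was conducted to ensure participant retention in the study", again with no exclusion.

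On timing, section 2.2 says that "Participants were only informed about which group they belonged to after baseline assessments", so missed sessions necessarily come after assignment. The Discussion explains that the pandemic "disabled the sample randomisation".

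Section 2.7 has two provisions that come near the issue. One is a check for attrition bias: "Comparative analyses between participants and dropouts will be realised by" t-test, Mann–Whitney, chi-squared or Fisher tests. The other is the use of weights, where needed, for unequal sampling probabilities. The article describes no analysis that retains the participants excluded for non-attendance.

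**The concern.** An analysis set defined by what participants did after assignment no longer compares the groups as assigned. Here the definition is also one-sided, because only people who were offered training sessions can fail it. A month's absence among adults aged 65 or older may reflect illness, injury, isolation or loss of motivation. The article itself anticipates comorbidities, records falls at each session, and reports that lockdown affected the intervention. If such absences are related to the outcome, the people concerned leave MT and SHD + MT while comparable people stay in SHD and CG.

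Four of the six pairwise comparisons set an exercise arm against a non-exercise arm, and these carry the conclusions about training, alone or combined with diet. The study already lacks randomisation, so this selection adds to whatever confounding the allocation brings, and it is avoidable.

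**Working it through.** **Step 1. The rule's own arithmetic.** At 3 sessions a week, 12 sessions take 12 / 3 = 4 weeks, which agrees with the month given in section 2.5.2. A 12-week programme has 12 × 3 = 36 sessions. More than 12 means at least 13 in a row, or 13 / 36 = 36% of the programme.

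**Step 2. Which arms can trigger it.**

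| Arm | Adherence record described | Exclusion from analysis |
|---|---|---|
| MT | session attendance | stated (2.5.2) |
| SHD + MT | session attendance, by the same programme; weekly food questionnaire | inferred from 2.5.3 |
| SHD | weekly food questionnaire | none stated |
| CG | weekly retention calls | none stated |

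The exposed comparisons are MT–SHD, MT–CG, SHD + MT–SHD and SHD + MT–CG. MT versus SHD + MT is exposed only if exclusion rates or reasons differ between those two arms. SHD versus CG is not affected.

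**Step 3. Possible size.** The documents give neither an exclusion rate nor a link between attendance and outcome, so both are assumed. Let a share q of an exercise arm, those with the lowest attendance, be removed, and let attendance correlate r with the change score. With no true effect and normal variables, the mean of those retained shifts by

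r × φ(z_q) / (1 − q) SD,

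where z_q is the q-quantile of the standard normal and φ its density. The multiplier φ(z_q)/(1 − q) is 0.195 at q = 10% and 0.350 at q = 20%.

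| q | r = 0 | r = 0.3 | r = 0.5 |
|---|---|---|---|
| 10% | 0 | 0.058 | 0.097 |
| 20% | 0 | 0.105 | 0.175 (just under) |

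The range is therefore about 0.06 to 0.17 SD. A negative r gives the same sizes in the opposite direction.

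**Step 4. Against the planned effect.** Section 2.3 uses an effect size of 0.40. Reading it as Cohen's f for four groups, with alpha 0.05 and power 0.80, a noncentral-F calculation needs 73 participants, or 76 when balanced (19 per arm). Allowing for 20% dropout gives 19 / 0.80 = 23.75, so 24 per arm against the stated 25, which supports the reading. The smallest spread between extreme means compatible with f = 0.40 is 2 × 0.40 = 0.80 SD. The illustrated shifts run from 0.058 / 0.80 = 7% to 0.175 / 0.80 = 22% of it.

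**Step 5. False-positive rate.** This was simulated with 25 per arm, no true effect, the lowest attenders removed from one arm and a two-sided t-test at 5%. With 5 of 25 removed, the rejection rate was 6.2% at r = 0.3 and 9.3% at r = 0.5. With r = 0 it stayed at 4.9%.

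**Step 6. Power.** With 20% dropout in every arm (80 completers), power is 84.5%. If the rule removed a further 10%, 20% or 30% of exercise-arm completers, power would be about 82.3%, 79.9% or 77.1% (equal-size approximation). The problem is mainly bias and much less loss of power.

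**The case against.** The case on the other side has several parts.

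- **Certainty and direction.** A reader might infer that every comparison with SHD and CG is biased, and in favour of exercise. The documents do not support that. If absence is unrelated to outcome, as absence caused by facility closures might be, there is no bias. The primary outcomes are many biomarkers plus untargeted metabolomics. Several, such as sodium, phosphorus and osmolality, have no single favourable direction, and healthier participants may have less room to improve.
- **Dropout allowance.** A reader might also infer that these exclusions consume the 20% dropout allowance in two arms. Section 2.3 does not say what the 20% covers.
- **Overlap with dropout.** Some people absent for a month may have no post-intervention sample. For them the rule changes nothing relative to an available-case analysis.
- **The model.** Step 3 trims the lowest attenders on a continuous scale, whereas the rule catches only unbroken absence. The upper corner of the range should not be quoted alone.
- **Silence of a condensed article.** That SHD has no exclusion rests on nothing being stated. A fuller document might contain a parallel rule or an all-assigned analysis.
- **No randomised comparison to protect.** Confounding by allocation may well be the larger threat.

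These points limit how strongly the concern can be put, and the first two rule out the stronger readings. They do not remove it. The exclusion is written without qualification and refers to the final analyses, so it is a stated choice and not a missing detail. The dropout comparison in section 2.7 can reveal attrition bias but does not correct it, and the article does not say whether excluded non-attenders count as dropouts. The weights address sampling probabilities, not attendance.

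**Conclusion.** The concern holds as one of exposure to bias. The article fixes a post-allocation, adherence-based exclusion that can act in MT and, by inference, SHD + MT, with no stated counterpart in SHD or CG. Nothing else in the article offsets it. Each comparison of an exercise arm with a non-exercise arm is open to selection bias of unknown size and direction. The figure of about 0.06 to 0.17 SD is an illustration that rests wholly on an assumed 10 to 20% exclusion and an assumed correlation of 0.3 to 0.5. It is not an estimate for this study. Section 2.7 puts the analyses in the future, so the rule can still be changed before they are run.

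**What to change.** In the main analysis, include every participant in the assigned group who has post-intervention data, regardless of attendance. Handle missing post-intervention values by one method common to all four arms, for example imputation from baseline variables recorded in every arm. Training attendance should not be in that common model, because it does not exist for SHD and CG.

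Keep the attendance rule only as a labelled per-protocol sensitivity analysis, preferably with a parallel compliance rule for the diet arms built from the weekly questionnaires. State explicitly that the rule applies to SHD + MT, if it does, and whether the 20% dropout allowance was meant to cover it. Report the number excluded, the reasons, and how many had post-intervention data, by arm.

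The cost is a change of wording and one additional analysis, plus the imputation work. The estimated exercise effect may be smaller, because it will reflect the attendance actually achieved. Data collection ended in December 2022, so excluded participants who were not re-measured can be recovered only by imputation, with the assumptions that this brings.

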#### 2.5.3. Combined Sustainable Healthy Diet and Multicomponent Training Group (SHD + MT) 

In this group, participants received the same SHD and MT interventions as the participants of the abovementioned groups: a weekly sustainable and healthy mixed food supply and the additional three group sessions (including the SHD culinary workshop) and one individual telephone interview, in addition to MT 50-min group sessions three times a week on non-consecutive days. 

#### 2.5.4. Control Group (CG)

The CG received advice on following habitual dietary and PA routines. During the project intervention period, one nutrition session regarding the main principles of a healthy diet and two low-intensity PA sessions were offered to the participants in this group. Weekly telephone contact was conducted to ensure participant retention in the study.

### 2.6. Outcome Assessments

#### 2.6.1. Primary Outcome

##### Blood-Based Biomarkers and Metabolic Alterations

Our primary outcomes concern blood-based biomarkers and metabolic alterations. At baseline and post-intervention, venous blood samples were taken. All the biochemical and metabolomic analyses—untargeted NMR—were performed in a certified laboratory. 

After an overnight fast of at least 8 h, a competent professional collected venous blood samples from the antecubital vein (required volume between 10 and 20 mL, maximum of two tubes) in a specially designated and equipped room, separating samples into serum and plasma. The following nutritional and age-related biomarkers [45] will be analysed in serum blood samples: glucose; fructosamine; insulin; cortisol; protein C-reactive (high sensitivity); vitamin B12; iron; sodium; phosphorus; calcium; magnesium; lipid profiles: total cholesterol, HDL-C, LDL-C, and triglycerides; and osmolality. Traditional biochemical parameters will be enzymatically measured [46]. LDL-C will be computed according to the Friedewald formula, estimated by subtracting HDL-C and one-fifth of the triglycerides value from the total cholesterol level [47]. 

We also intend to perform untargeted NMR-based metabolomics analyses. Plasma samples were immediately frozen at −80 °C and will remain so until analyses are conducted. Blood plasma preparation for NMR analyses will include adding saline solution (sodium chloride (NaCl) 0.9%, 10% deuterium oxide) to plasma, followed by centrifugation and transfer to 5-mm NMR tubes. The NMR analyses will be performed in a Bruker Avance III HD 600 MHz spectrometer (Bruker BioSpin, Rheinstetten, Germany) equipped with a cryoprobe using a Carr–Purcell–Meiboom–Gill (CPMG or T2-edited) pulse sequence (cpmgpr1d) [48]. For one representative sample, 2D spectra (heteronuclear single quantum coherence (HSQC) and total correlation spectroscopy (TOCSY)) will be acquired to aid in metabolite annotation.

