According to the socio-ecological model, an individual’s behaviour is affected by and affects the social environment. Therefore, holistic interventions are more practical in addressing healthy ageing [29]. Environmental factors may have an essential role in the modulation of food and physical activity (PA) habits [30]. Food, such as availability and accessibility to supermarkets, grocery or convenience food stores, and restaurants [30], and PA, such as details on walkability, parkland use, access to PA facilities [30,31], and environmental features must be considered. The use of Geographic Information Systems (GIS) can provide a novel and better understanding of the available environmental features, contributing to the implementation of effective healthy ageing policies [29].

Therefore, our primary aim is to assess the effect of different SHD and MT interventions on the biochemical and metabolic profiles, nutritional statuses and adequacy, physical fitness, body composition and anthropometry, cognitive function, and quality of life of older adults through a quasi-experimental study. Additionally, as a secondary aim, we intend to characterise food and PA environmental features and study their potential role in the modulation of food and PA practices.

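### Sixteen serum biomarkers plus NMR metabolomics are all primary, and the stated correction works only within each variable, so the 5% alpha used for the sample size does not hold across the primary outcomes

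*Protocol article*

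**What the plan says.** Section 2.6.1, headed as the primary outcome, opens with "Our primary outcomes concern blood-based biomarkers and metabolic alterations". The serum panel is "glucose; fructosamine; insulin; cortisol; protein C-reactive (high sensitivity); vitamin B12; iron; sodium; phosphorus; calcium; magnesium", followed by "lipid profiles: total cholesterol, HDL-C, LDL-C, and triglycerides; and osmolality". That is 11 + 5 = 16 analytes. The same section adds "We also intend to perform untargeted NMR-based metabolomics analyses". No analyte and no spectral variable is named as the one on which the trial will be judged.

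Section 2.7 sets one significance level for the whole plan: "The minimum threshold value for statistical significance used will be" 0.05. Each dependent variable gets a repeated-measures ANOVA, or a non-parametric counterpart, for main effects and interactions. The multiplicity step is: "When significant interactions are found, Bonferroni posthoc tests will determine the origin of the differences". For NMR, the same section uses multivariate analysis to find the peaks that best separate the groups, then tests that panel univariately. It names no correction there.

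Section 2.3 sizes the trial with an effect size of 0.40, alpha 0.05, beta 0.20 and 20% dropout, giving 25 per group and at least 100 in total.

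**The concern.** The Bonferroni step limits error among the pairs of groups for one biomarker, once that biomarker has shown a significant interaction. It does nothing about there being 16 biomarkers, each with its own chance of passing the 0.05 gate. With no biomarker singled out, any of the 16, or any NMR peak, could be reported as a significant primary effect.

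At stake is the meaning of a positive primary result. The sample size presents the trial as having a 5% false-positive risk and 80% power. Both figures describe one test of one outcome, not the family that section 2.6.1 defines as primary. The study is also non-randomised, so a chance finding would be harder to tell from a real effect or from baseline imbalance.

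**Working it through.** **1. Reproduce the plan's sample size.** Inputs from section 2.3: four groups, effect size 0.40 (read as Cohen's f), alpha 0.05, power 0.80, 20% dropout. Method: noncentral F with 3 numerator degrees of freedom and noncentrality f²N = 0.16N. The smallest N with at least 80% power is 73, or 76 when balanced (19 per group). Inflating for dropout, 19/0.8 = 23.75, so 24 per group and 96 in total. The stated 25 per group and at least 100 is slightly conservative. The calculation therefore matches **one** test at alpha 0.05.

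**2. Family-wise error if the 16 tests were independent.**
- 1 − 0.95^16 = 0.560.
- Expected false positives: 16 × 0.05 = 0.8. This expectation does not depend on the correlation.

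**3. Allow for dependence.** The markers are not independent. For one, "LDL-C will be computed according to the Friedewald formula", which makes it a function of total cholesterol, HDL-C and triglycerides. The article gives no correlations, so these are assumed. Simulation of four-group ANOVAs under the global null, 20 per group, one group test per marker (with two time points, the group-by-time test is a one-way ANOVA on change):

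| Assumed common correlation | Chance of at least one false positive |
|---|---|
| 0 (formula) | 0.56 |
| 0.1 | 0.55 |
| 0.2 | 0.52 |
| 0.3 | 0.47 to 0.49 |
| 0.5 | 0.39 |
| 0.7 | 0.27 to 0.29 |

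Where two values are shown, separate simulations differed by that much. Building LDL-C from its components and tying osmolality to sodium and glucose, with background correlation of 0 to 0.2, gives 0.53 to 0.50. As a cross-check, about 10 effective independent tests gives 1 − 0.95^10 = 0.401, close to the value at correlation 0.5.

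**4. What a correction across the 16 would do.**
- Strictest step: 0.05/16 = 0.003125. Family-wise error if independent: 1 − (1 − 0.003125)^16 = 0.049.
- Completers: 100 × 0.8 = 80. Noncentrality: 0.16 × 80 = 12.8. With a one-covariate ANCOVA, the denominator has 80 − 4 − 1 = 75 degrees of freedom.
- Power at 0.05: 0.845. Power at 0.003125: 0.492.
- For scale, 80% power at 0.003125 would need 124 completers, or 124/0.8 = 155 enrolled.

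**5. NMR.** The number of spectral variables is not given. Peaks are chosen because they separate the groups and are then tested for group differences in the same participants. Such selection keeps the smallest p-values, so it offers no protection. The added error is real but cannot be sized from the article.

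**The case against.** **Is this only silence that an analysis plan would fill?** An article condenses, and the analysis plan is not shown. Section 2.7 calls 0.05 a minimum threshold, and its Bonferroni step shows that multiplicity was considered. This carries some weight: the article never says that error across outcomes will be left uncontrolled. But it does more than stay silent. It fixes a primary outcome with many components, a threshold, a test for each variable and a correction at a level that does not cover the family. A plan that controlled error across outcomes would have to depart from the stated 0.05 rule, and the power in section 2.3 would no longer apply.

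**Is a false-positive primary result more likely than not?** A reader might infer this from the 56%. The documents do not support it for the serum panel. The figure needs independence, which the derived LDL-C rules out, and it falls below one half at a common correlation of about 0.3. Adding NMR peaks could push it back above one half: 50 extra tests give 0.86 at correlation 0.3 and 0.70 at 0.5. But that count and those correlations are assumed.

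**Is every NMR signal tested at 0.05?** A reader might infer this too. Section 2.7 instead tests a panel that has already been selected by multivariate analysis. The weakness there is selection and testing on the same data.

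**Does the article contradict itself on what is primary?** The Introduction puts "biochemical and metabolic profiles, nutritional statuses and adequacy, physical fitness, body composition and anthropometry, cognitive function, and quality of life of older adults" under its primary aim, while section 2.6.2 treats most of these as secondary. That is loose wording. The Abstract and section 2.6.1 agree that the primary outcomes are the blood biomarkers and the metabolic profile.

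**Conclusion.** The point holds. The primary family is 16 serum biomarkers plus an NMR metabolome, and the only correction acts within a variable. If no intervention affects any marker, the chance of at least one false-positive primary result from the serum panel is roughly 27% to 56%. Even the low end is more than five times the 5% in section 2.3.

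This range rests on one group test per marker, the global null and assumed common correlations from 0.7 down to 0. Testing main effects as well as interactions, which section 2.7 also plans, is not counted and would not lower it. The NMR contribution comes on top and is not quantified.

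**What to change.** - **Serum panel.** Declare the 16 biomarkers one primary family and judge the group-by-time effect on Holm-adjusted p-values. Benjamini-Hochberg is an alternative only if false discovery rate control is stated as the goal. The two are not interchangeable, because Benjamini-Hochberg does not control family-wise error once some markers truly respond. Run the Bonferroni group comparisons only for biomarkers that pass.
- **NMR.** Label the metabolomic analysis exploratory and apply false discovery rate control across all spectral variables, not only the selected panel.
- **Power.** State that the 80% in section 2.3 applies to a single outcome at alpha 0.05. Report that at the strictest step (0.05/16), power for f = 0.40 with 80 completers is about 49% under a one-covariate ANCOVA. The repeated-measures model in section 2.7 may give a different figure.

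The cost is some wording, adjusted p-values and lower power per biomarker. No added enrolment is proposed, since section 2.1 says that data collection ended in December 2022. Section 2.6.1 describes the assays in the future tense, so as the article stands the rule could still be fixed before analysis.
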